##### Quality of life

is assessed by the Quality of Life Assessment Scale developed by the WHO, WHO-QoL-Bref, comprising 26 items (WHOQOL Group 1998; [31]).

##### Social support

To assess the possible impact of social ties and support on the outcome, the Berliner Social Support Scales BSSS [32] are used. The domains of support to be rated by the patient are: perceived available support (8 items), need for support (4 items), support seeking (5 items) and support actually received from the person closest to the patient (15 items).

##### Internalised stigma

Internalised stigma, or self-stigma, is assessed using the 29-item Internalised Stigma of Mental Illness Inventory [33]. Self-esteem, typically impaired by internalised stigma, is examined by the 10-item Rosenberg Self-Esteem Scale [34]. The cognitive appraisal of stigma as a stressor (i.e., whether perceived harm due to stigma exceeds perceived coping resources) is measured by the 8-item Stigma Stress scale [35,36]. Finally, four items assess shame and contempt as emotional reactions to compulsory admission.

#### Data preparation and data entry

Data entry is done by a research assistant at the coordinating centre. Quantitative data from all centres are entered immediately after data collection and checks of completeness and validity of data are performed regularly.

A cost catalogue for each service used by the patients will be compiled. To estimate comprehensive client-level care costs for each study patient, detailed information about frequency and duration of contact with health, social and other services provided by public organisations is recorded. Unit costs (per appointment, hospital per diem rate etc.) will be adjusted according to the frequency with and the duration for which each patient used each service as recorded in order to calculate the total cost of services and subtotals associated with various groups of component services and to compare the cost of support in standard care with that of the new intervention.

#### Data analysis and statistical power

All major endpoints of the study will be compared between the intervention and the control group. Primary outcome of the study is the time in hospital accumulated over all involuntary inpatient stays during the 24 month period. This outcome criterion will be analysed in terms of both “time in hospital” and savings of health care budgets (“health care costs”).

As further endpoints of the study (secondary outcome criteria) changes in the perspective of the patients are assessed. Hypothesised benefits of the intervention are a reduction of institutionalised care and coercion. Lower levels of subjectively experienced coercion are supposed to be associated with a respective increase in quality of life, treatment satisfaction and level of empowerment.

To address the major research questions, the quantitative outcome data will be analysed for the whole trial across the four centres, using General Linear Models. T-tests for independent samples are applied primarily to test the comparability of the intervention and the control group. Analyses of covariance are performed to compare the intervention and the control group with respect to the primary outcome (time in hospital accumulated over all involuntary inpatient stays) and secondary outcomes (reduction in levels of subjectively experienced coercion; increase in quality of life, treatment satisfaction and level of empowerment). Age, gender, centre and other variables which show significant between-group differences are included in the GLM models as covariates. To examine which characteristics on the patient level (treatment history, diagnosis, social network, treatment adherence in the two-year follow-up) modify the outcome, we examine the effects of these variables on the outcomes of interest within the intervention group, applying regression analyses. The level of significance is set at 0.05, two-tailed.

The planned overall sample size across all centres is 400 patients, of which 200 each will be assigned to the intervention group or to the control group. So each centre is expected to contribute 100 patients (50 intervention group and 50 control group).

Power analyses revealed that these sample sizes will be large enough to identify significant differences in the primary outcome criterion (length of compulsory inpatient episodes) between the intervention and the control group. For power analysis, length-of-stay data from the Psychiatric University Hospital Zurich over the period 2007–2008 were used. Compulsorily admitted patients (with the same diagnostic spectrum and age range as the sample considered for inclusion) stayed a mean length of 33 days (SD 42 days; CV 1.25) during a 24-month period. A log-normal distribution for the length of stay was assumed. A two-sample t-test on the mean ratio was performed to calculate the sample size on the basis of these data. The probability of type I error was set at 5% and probability of type II error at 20%. An 8–day reduction of the mean length of compulsory inpatient time due to the study intervention (approximating a quarter of inpatient time) was considered a clinically relevant difference. For confirming a reduction of the mean length of compulsory inpatient time from 33 days to 25 days a sample size of 193 in each (intervention and control) group would need to be treated (total sample size of 386).

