## Methods

### Aims

The study has three main goals:

1) To evaluate the effectiveness of an intervention that aims to prevent compulsory admission to psychiatric hospital treatment and to reduce the time in hospital in connection with compulsory inpatient episodes (primary outcome criterion)

2) To evaluate changes in the perspective of the patients, hypothesizing that the intervention changes patients’ perceived coercion so that they feel less coerced and increases patients’ empowerment, quality of life and treatment satisfaction (secondary outcome criteria)

3) To examine which characteristics on the patient level (treatment history, diagnosis, social network, treatment adherence in the two-year follow-up) modify the outcome.

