### Measurements

At baseline (t0) and again after 12 (follow-up t1) and 24 months respectively (follow-up t2), data on patient characteristics and health care use are gathered by means of face-to-face interviews and questionnaires. Interviews with study participants (intervention and control patients) are conducted by the members of the study staff.

Baseline assessment is scheduled upon discharge from the index episode at one of the study centres. Additional data concerning individual risk factors and service utilisation are collected during the monthly telephone contacts between the patient and his/her personal mental health care worker (intervention group).

As the overall number of questions at baseline assessment is high, a limited number of scales will be applied at the t1- and t2-follow-ups to limit the burden on patients and to comply with restricted time resources available for the interview session. Table 1 provides an overview of the measurements and the instruments used at the different time points.

**Table 1 T1:** Outcome measures

**Variables**	**Instrument**	**Time of assessment**
Sociodemographic data	Patient file; CSSRI-EU	t0, t1, t2
Utilisation of mental health care or other relevant services (Previous health care use; number and length of voluntary and involuntary psychiatric inpatient episodes; frequency and length of stays in forensic facilities, frequency of use of outpatient psychiatric care and of other services during follow-up)	CSSRI-EU	t0, t1, t2 continuously in the intervention group; every 3 months in the control group
Psychopathology	CGI; GAF; OQ- 45; BPRS	t0, t1, t2
Risk of self-harm or threat to others	Patient file; HCR-20; PCL-SV; BPRS	t0, t1, t2
Informal coercion/perceived coercion	MacArthur AES	t0
Empowerment	Empowerment-Scale	t0, t1, t2
Treatment satisfaction	CSQ-8	t0, t1, t2
Quality of life	WHO-QoL-Bref	t0
Social support	BSSS	t0
Internalised Stigma	Internalised Stigma of Mental Illness Inventory	t0, t1, t2
Self-esteem; Cognitive appraisal of stigma as a stressor; Emotional reactions to compulsory admission	Rosenberg Self-Esteem Scale; Stigma-Stress Scale; 4 items	t0

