##### Perceived coercion / informal coercion

To assess the patients’ perceptions of coercion during their admission to psychiatric hospital, the MacArthur Admission Experience Survey AES [26] is applied (short form; 15 items). Additionally, perceptions of the fairness and effectiveness of coercive measures and methods of informal coercion are assessed [27,28]. Informal coercion includes negative pressures and threats as to the use of legal actions, as well as threats concerning the execution of payments, housing restrictions and the right to child custody. All coercion questions are presented on a dichotomous true/false scale. At t1 and t2 follow ups the MacArthur Admission Experience Scale, modified for outpatient use, will be applied.

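### Quality of life is a secondary outcome, yet its only named instrument is scheduled at baseline alone; for perceived coercion, Table 1 and the text disagree on follow-up

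*Protocol article*

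**What the plan says.** **Outcomes.** In the protocol article, the second aim under Aims hypothesises that the intervention makes patients feel less coerced and "increases patients’ empowerment, quality of life and treatment satisfaction (secondary outcome criteria". Under Data analysis and statistical power, "changes in the perspective of the patients are assessed" as further endpoints, and the arms are to be compared by analysis of covariance on "secondary outcomes (reduction in levels of subjectively experienced coercion; increase in quality of life, treatment satisfaction and level of empowerment". The Discussion again lists quality of life and perceived coercion among the measures of effectiveness.

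**Schedule.** Two rows of Table 1 (Measurements) read "Quality of life WHO-QoL-Bref t0" and "Informal coercion/perceived coercion MacArthur AES t0". The rows for empowerment and treatment satisfaction carry t0, t1 and t2. The text before the table explains that "a limited number of scales will be applied at the t1- and t2-follow-ups to limit the burden on patients".

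**Instruments.** The Quality of life paragraph names the WHO-QoL-Bref (26 items) and gives no time points. The Perceived coercion / informal coercion paragraph says that, for perceptions of the hospital admission, "the MacArthur Admission Experience Survey AES [26] is applied (short form; 15 items". It then adds: "At t1 and t2 follow ups the MacArthur Admission Experience Scale, modified for outpatient use, will be applied". The Psychopathology paragraph lists quality of life as one of four self-rated domains of the OQ-45.2, which Table 1 schedules at t0, t1 and t2.

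**The concern.** An outcome needs a measurement after the intervention has had time to act. For quality of life, the aims, the analysis section and the Discussion all promise a treatment comparison, but the schedule collects the named instrument only at baseline. An analysis plan written later cannot repair this, because it cannot supply questionnaires that were never given.

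For coercion, the table and the text disagree on whether anything is measured at follow-up. Staff who work from Table 1 would collect nothing after t0. Staff who work from the text would collect an outpatient form that differs from the baseline form. The outcome is also worded as a reduction in levels, which invites subtracting one form from the other.

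**Working it through.** **1. The plan's own figure.** The only computed figure is the primary sample size, 193 per group. Inputs from the power paragraph: CV 1.25, means 33 and 25 days, two-sided 5%, power 80%, log-normal.
- σ² = ln(1 + 1.25²) = ln(2.5625) = 0.941
- δ = ln(33/25) = 0.2776
- n = 2 × (1.960 + 0.842)² × 0.941 / 0.2776² ≈ 192 per group by the normal approximation; 193 with the noncentral t (power 0.801)

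The figure reproduces. Nothing below bears on it.

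**2. Named secondary outcomes against the schedule.**

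| Outcome | Named instrument | Table 1 | Instrument text |
|---|---|---|---|
| Perceived coercion | MacArthur AES | t0 | outpatient-modified form at t1, t2 |
| Quality of life | WHO-QoL-Bref | t0 | no times given |
| Treatment satisfaction | CSQ-8 | t0, t1, t2 | no times given |
| Empowerment | Empowerment-Scale | t0, t1, t2 | no times given |

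Quality of life has 0 of 2 follow-up visits with its instrument, and no other section adds one. Coercion has 0 of 2 if Table 1 governs and 2 of 2 if the text governs. The other two outcomes are complete.

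**3. What different forms do to the coercion analysis.** Suppose the outpatient form differs from the admission form by an unknown shift k.
- Within one arm: follow-up minus baseline = true change + k. Since k is unknown, this difference cannot be read as a reduction in coercion.
- Between arms at follow-up: (mean, intervention + k) − (mean, control + k). The shift cancels.

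The planned comparison therefore needs the same form in both arms at follow-up, not the same form as at baseline. The covariates the article names are age, gender, centre and variables that differ significantly between groups; a baseline coercion score is not named.

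A simulation illustrates this. Assumptions, not from the documents: true difference −0.30 SD, baseline-to-follow-up correlation 0.5, the two measures on different scales. With 200 per arm and 2,000 runs, analysis of covariance gave a mean estimate of −0.301 (empirical SE 0.089).

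**4. Precision for coercion on the outpatient form.** With 200 per arm, 5% two-sided and 80% power, the detectable difference in SD units is 2.802 × √(2/200) × √(1 − r²), where r is the assumed correlation of the t0 AES with the follow-up form:
- r = 0 (no baseline adjustment): 0.28
- r = 0.3: 0.27
- r = 0.5: 0.24

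These assume complete follow-up. A baseline on a different form can still help as a covariate.

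**The case against.** **Table 1 may simply be incomplete.** It omits the follow-up coercion form that the text specifies, so it could also omit the WHO-QoL-Bref at follow-up. The Quality of life paragraph does not confine the instrument to baseline, and the Discussion promises assessment of patients' perceptions at 12 and 24 months. This is possible. But the article says the follow-up battery was cut on purpose, the rows for empowerment and satisfaction carry all three times, and no section places the WHO-QoL-Bref after t0. Whether the cause is an omission or a deliberate cut, the schedule must be corrected.

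**Quality of life is not wholly unmeasured at follow-up.** The OQ-45 domain is collected at every visit, so it would be wrong to say that no related follow-up data exist. That stands. The domain sits under psychopathology, however, and is nowhere designated as the quality-of-life outcome; relying on it would itself change the plan.

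**Changing the coercion form is defensible.** The baseline form concerns the hospital admission, and a patient not readmitted would have no new admission to rate. This stands too. A reader might infer from the change of form that the coercion effect cannot be estimated, and so that two of the four secondary outcomes are lost. The documents do not support that. The named analysis is a comparison of arms, the Study design section applies t1 and t2 to both groups, and nothing restricts the outpatient form to one of them. Only a change-from-baseline reading fails.

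**Conclusion.** The point holds in two parts of unequal weight.

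- **Quality of life:** one of four named secondary outcomes has no follow-up value on its named instrument. As written, its treatment effect cannot be estimated at any sample size. This rests only on Table 1 being followed as printed.
- **Perceived coercion:** the schedule contradicts itself. If the text governs and both arms receive the outpatient form, the between-arm effect is estimable. If Table 1 governs, there are no follow-up data. In neither case can a drop from the admission form to the outpatient form be read as less coercion.

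Treatment satisfaction, empowerment, the primary outcome and the 193 per group are unaffected.

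**What to change.** 1. **Quality of life.** Schedule the WHO-QoL-Bref at t1 and t2 for both arms and correct Table 1. The cost is 26 items at each of two existing face-to-face visits, a small added burden on patients. If that is too much, either name the OQ-45 quality-of-life domain as the measure, at no extra collection, or remove quality of life from the secondary outcomes. The choice must be made before follow-up visits take place, because missed questionnaires cannot be recovered.
2. **Coercion schedule.** Enter the outpatient-modified AES in Table 1 at t1 and t2, for both arms, so that it agrees with the instrument text. This costs one table row.
3. **Coercion outcome.** Define it as the between-arm difference in the outpatient-form score at t1 and t2, with the t0 AES as a covariate only, and replace the reduction wording, which can be read as change from baseline. This is a wording change. The covariate should be recorded before the instruction sessions start: Measurements places baseline upon discharge, whereas Intervention places the sessions before discharge, so the order should be stated.

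### Extra covariates for the primary ANCOVA are chosen by significant group differences, so prior involuntary inpatient use, recorded at t0, enters only by chance imbalance

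*Protocol article*

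**What the plan says.** All references are to the protocol article.

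- **Outcome and model** (Data analysis and statistical power): "Primary outcome of the study is the time in hospital accumulated over all involuntary inpatient stays during the 24 month period". "Analyses of covariance are performed to compare the intervention and the control group with respect to the primary outcome", within General Linear Models; the secondary outcomes are handled the same way.
- **Comparability check** (same section): "T-tests for independent samples are applied primarily to test the comparability of the intervention and the control group". The variables to be tested are not listed.
- **Covariate rule** (same section): after naming age, gender and centre, the sentence continues that "other variables which show significant between-group differences are included in the GLM models as covariates".
- **Level** (same section): "The level of significance is set at 0.05, two-tailed".
- **Prior use is recorded** (Measurements, Table 1): the CSSRI-EU row, with t0 among its time points, covers "Previous health care use; number and length of voluntary and involuntary psychiatric inpatient episodes". The text on health care use says that the same inventory gives treatment history.
- **Planned use of treatment history** (Data analysis and statistical power): it is listed among possible modifiers, of which the article says "we examine the effects of these variables on the outcomes of interest within the intervention group, applying regression analyses". It is not a named covariate in the comparison of the two groups.

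**The concern.** In a randomised trial, a significant difference in a variable fixed before allocation is a chance event. A rule that adds covariates on that basis has three faults.

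1. It selects for imbalance. A variable unrelated to outcome can enter, while a strongly prognostic one stays out in about 95% of trials.
2. The primary model is not known until the groups have been compared, and the list of candidates is open.
3. An imbalance in a prognostic variable that falls just short of significance is left in the treatment estimate.

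Prior involuntary inpatient use is the clearest case. It is the pre-entry counterpart of the primary outcome and it is already collected, yet it enters the primary model only if it happens to differ between groups. At stake are precision and protection against chance imbalance in the main result.

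**Working it through.** **Inputs from the article (Data analysis and statistical power):** mean 33 days reduced to 25; CV 1.25; log-normal length of stay; two-sided 5%; 80% power; 193 per group calculated, 200 per group planned.

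**Assumed:** r, the correlation of prior with follow-up involuntary days on the log scale. The documents give no value, so a range is shown.

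**1. Reproduce the plan's figure.** Log-scale effect |ln(25/33)| = 0.2776. Log-scale SD = √ln(1 + 1.25²) = 0.970. A two-sample t-test (noncentral t) needs 193 per group, which matches. Power at 200 per group is 0.816. The calculation uses no covariate.

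**2. How often the rule acts.** A single variable tested at 5% enters in 5% of trials (simulated 4.8% to 5.2%). With k independent tests, the chance that at least one enters is 1 − 0.95^k: 40% for k = 10 and 64% for k = 20. Both k and independence are assumptions.

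**3. What a fixed covariate would give.** The residual SD becomes 0.970 × √(1 − r²).

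| r | n per group for 80% power | Power at 200 per group |
|---|---|---|
| 0 | 193 | 0.816 |
| 0.1 | 191 | 0.820 |
| 0.3 | 176 | 0.851 |
| 0.5 | 145 | 0.911 |
| 0.6 | 124 | 0.947 |

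**4. Simulation of the rule.** 20,000 trials per scenario, 200 per group, one covariate, normal on the log scale.

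| r | Power: never adjust | Power: the rule | Power: always adjust | Type I error: the rule |
|---|---|---|---|---|
| 0.1 | 0.814 | 0.814 | 0.818 | 0.050 |
| 0.3 | 0.813 | 0.817 | 0.849 | 0.050 |
| 0.5 | 0.815 | 0.826 | 0.907 | 0.041 |
| 0.6 | 0.814 | 0.829 | 0.944 | 0.040 |

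The rule captures little of the available gain. Its type I error falls below 5% at higher r because the trials left unadjusted are those with smaller imbalance, while their standard error still allows for the full range.

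**5. An imbalance that just misses significance.** Take a baseline difference of z = 1.9, so the covariate stays out. The standard error of the unadjusted log difference is 0.970 × √(2/200) = 0.0970, and the estimate shifts by r × 1.9 × 0.0970.

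- r = 0.3: shift 0.055, which is 20% of the planned effect of 0.2776.
- r = 0.5: shift 0.092, which is 33%.

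Given that imbalance, the unadjusted test statistic under the null has mean 1.9r and variance 1 − r². The chance that it exceeds 1.96 in absolute value is 5.3% at r = 0.1, 7.7% at r = 0.3 and 12.2% at r = 0.5. These rates are conditional on the imbalance; averaged over all trials, the error stays at or below 5%, as step 4 shows.

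**6. Timing of t0.** Under Intervention, the first instruction sessions follow immediately on randomisation and take place before discharge. Under Measurements, baseline assessment is scheduled upon discharge. Some t0 ratings may therefore follow the first sessions. The covariate rule is not limited to pre-randomisation values, so a scale already changed by the sessions could be selected because it differs between groups, and adjusting for it could remove part of the effect.

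**The case against.** The strongest reply is that the plan is sounder than it may look. On the natural reading, age, gender and centre are named in advance and only the remaining variables are data-driven. That stands, although the sentence can also be read as putting the condition on all of them. The article also does not say outright that the comparability t-tests are the selection step; that link is plausible but inferred. A full covariate list may properly sit in an analysis plan that is not shown. That would answer a complaint of omission, but here the article states a selection rule.

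A reader might infer more than the documents support:

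- **That the primary test has an inflated error rate.** The simulation does not bear this out: 0.040 to 0.050 overall.
- **That the trial is short of power for this reason.** The 193 per group reproduces without any covariate, and 200 are planned. The gain from adjustment is forgone, not a deficit in the calculation.
- **That prior involuntary days are the strongest predictor.** Nothing in the article ranks predictors. Every participant must have had a compulsory admission in the past 24 months, and this restriction could lower r.
- **That t0 records exactly the preceding 24 months.** That window belongs to the eligibility criteria; no look-back period is given for the inventory.
- **That the model is settled after unblinding.** The article does not say when it is locked.

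The 40% to 64% figure is also limited: baseline variables are correlated, and it counts how often a covariate is added, not the bias that results.

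**Conclusion.** The point holds in a limited form. Choosing the additional covariates by significant group differences is a poor rule in a randomised trial, and it leaves prior involuntary inpatient use out of the primary model in about 95% of trials.

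The size depends on r, which is assumed. The rule gives up about 3 points of power at r = 0.3 (0.817 against 0.849), 8 at r = 0.5 (0.826 against 0.907) and almost nothing at r = 0.1. The conditional bias from a near-significant imbalance grows with r in the same way. These figures rest on the article's log-normal assumption and on a single covariate.

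The plan is not invalidated: overall type I error and the sample size calculation are both intact. This should be changed because the better rule costs almost nothing.

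**What to change.** Delete the significance-driven rule and state instead:

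*The primary ANCOVA includes centre (as a factor), age, gender and involuntary inpatient days before the index admission, over the look-back recorded at t0 and on the same scale as the outcome, regardless of baseline differences. No covariate is selected by significance testing.*

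This wording also removes the doubt about whether age, gender and centre are unconditional. Comparability tables may stay as description.

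Add that covariates are limited to values that the intervention cannot have affected. For the scales rated at t0, including those behind the secondary outcomes, the authors should first establish whether the rating precedes the first instruction session; if it may not, it should not be treated as a pre-randomisation value.

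The cost is one or two sentences in the analysis section. The primary model needs no new data, because prior involuntary use is already recorded; only the look-back has to be written down.

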**Figure 1 F1:**
[figure not shown]
Flowchart.

The intervention is applied during a 24-month period. In both, the intervention and the control modality patients receive treatment as usual, i.e. regular out- or inpatient mental health care as offered in the respective study region.

The study encompasses a baseline assessment during the inpatient episode (t0) and a one-, respectively two-year follow-up (t1; t2). This applies to both the intervention and the control group. To enhance the compliance to contacts and assessments, each study participant (in the intervention and in the control group) receives an expense allowance of 60 CHF that is paid in instalments of 10 CHF at t0 and 25 CHF each at t1 and t2.

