## Discussion

The current study aims to prevent compulsory admission to psychiatric hospital and to reduce patients’ perceived coercion by offering an intervention programme consisting of individualised psycho-education and a 24-month preventive monitoring after inpatient admission. The intervention hereby intends to increase patient satisfaction, quality of life and empowerment in patients with serious mental disorders and previous compulsory psychiatric admission(s). Detailed follow-up assessments of service use, psychopathology and patients’ perceptions are scheduled 12 and 24 months after discharge. The intervention programme will be compared with standard care procedures in order to prove its effectiveness (in terms of “time in hospital” in connection with involuntary inpatient episodes, perceived coercion, empowerment, treatment satisfaction, quality of life) and cost-effectiveness (in terms of cost-containment in inpatient mental health care). Moreover the study seeks to identify individual and social factors that influence primary and secondary outcomes.

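### Aim 3 is analysed in the intervention group alone, so it cannot separate characteristics that alter the programme's effect from those that are merely prognostic

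*Protocol article*

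**What the plan says.** Under Aims, the third goal of the protocol article is "To examine which characteristics on the patient level (treatment history, diagnosis, social network, treatment adherence in the two-year follow-up) modify the outcome". The section Data analysis and statistical power repeats the question and fixes both population and method: "we examine the effects of these variables on the outcomes of interest within the intervention group, applying regression analyses". It mentions no treatment-by-characteristic interaction and no parallel model in controls, and neither appears elsewhere in the article. The Discussion restates the goal more loosely: "Moreover the study seeks to identify individual and social factors that influence primary and secondary outcomes".

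Controls are not short of the data that matter here. Of the baseline and follow-up assessments, Study design says "This applies to both the intervention and the control group", and under Measurements "Interviews with study participants (intervention and control patients) are conducted by the members of the study staff". Table 1 lists previous health care use and social support at baseline. The section on patient characteristics takes diagnosis from the index-episode file.

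**The concern.** Asking what modifies an outcome in a trial of a programme naturally reads as asking who gains more or less from it. That is a contrast between arms. A variable that predicts involuntary days among treated patients may predict them just as strongly among controls, and the stated analysis has no means of telling. Patients with many earlier admissions, for instance, might do worse under any care. A treated-only regression would show that association and could be taken to mean that the programme works less well for them. The reverse can also happen: a real modifier may be hidden because it offsets a prognostic association in the treated arm.

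One of the four listed variables has a separate difficulty. Adherence over the two follow-up years arises after randomisation, and the programme sets out to change it: the end of the Background, the psycho-education paragraphs under Intervention and the limitations section all name better adherence or compliance as a target. It is a possible mediator, yet it is listed alongside baseline traits.

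**Working it through.** **The plan's own figure.** Inputs from Data analysis and statistical power: mean 33 days, CV 1.25, log-normal stays, target 25 days, two-sided 5%, power 80%.

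- σ = √ln(1 + 1.25²) = 0.970; δ = |ln(25/33)| = 0.278
- n = 2(1.960 + 0.842)²σ²/δ² = 192 per group by the normal approximation; the noncentral t gives 193, the stated figure.

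The sample size reproduces. It has no bearing on this point except to supply a working scale.

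**What the one-arm coefficient estimates.** Write log days = μ + θT + βX + γTX, with T the arm and X the characteristic. The slope on X is β in controls and β + γ in treated patients. Modification is γ, the difference between the two slopes. The planned regression estimates only the sum β + γ.

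**Purely prognostic factor (γ = 0).** Assumptions: 200 per arm, X binary and evenly split, β over a range because the documents give none. The standard error is 0.970 × √(2/100) = 0.137 within the treated arm and 0.970 × √(4/100) = 0.194 for the interaction. A simulation of 20,000 trials gives these shares significant at 0.05:

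| β (log scale) | Treated arm only | Two-arm interaction |
|---|---|---|
| 0 | 5% | 5% |
| 0.10 | 11% | 5% |
| 0.20 | 30% | 5% |
| 0.278 (size of the planned effect) | 52% | 5% |
| 0.40 | 83% | 5% |
| 0.50 | 95% | 5% |

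Hand check at 0.40: 0.40/0.137 = 2.92, and Φ(2.92 − 1.96) = 0.83.

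For a continuous factor, Fisher's z with n = 200 gives:

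- r = 0.2: atanh(0.2) × √197 = 2.85, power about 81%
- r = 0.3: atanh(0.3) × √197 = 4.34, power about 99%

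The two sets agree. An evenly split binary factor has r = (β/2)/√(σ² + β²/4), which is 0.05, 0.20 and 0.25 at β = 0.10, 0.40 and 0.50. At r = 0.2 they give 83% and 81%.

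**True modifier masked by prognosis (γ = −β).** For sizes 0.278, 0.40 and 0.50 the treated-only analysis is significant about 5% of the time. The interaction test is significant 30%, 54% and 73% of the time.

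**True modifier with no prognostic role (β = 0, γ = 0.278).** The treated-only analysis detects it 52% of the time and the interaction test 30%. The extra power comes from assuming that the control slope is zero, which the treated arm alone cannot check.

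**If only prognosis is meant.** With a common slope, both arms together give a standard error of 0.970 × √(2/200) = 0.097 instead of 0.137. Dropping controls widens the interval by a factor of √2.

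**Price of the interaction test.** For γ = 0.278: 0.278/0.194 = 1.43, and Φ(1.43 − 1.96) = 0.30. The interaction detectable with 80% power is 2.802 × 0.194 = 0.54, about twice the planned effect. Detecting 0.278 would need 8σ²(2.802)²/δ² ≈ 767 per arm.

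**The case against.** The wording concerns modifying the outcome, not the treatment effect, and the Discussion speaks of factors that influence outcomes. On a prognostic reading, regression within the programme asks a coherent, narrower question: who does well or badly under it. That reading is open and cannot be dismissed. It leaves the choice of one arm unexplained, though, since controls carry the same baseline information and the same outcome.

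A reader might infer that the trial will credit the programme with prognostic associations, or will pick out the wrong patients as benefiting. The documents do not say so. No section states that results for this aim will support claims of differential benefit. The remark in the limitations section about which patients might qualify for the programme belongs to the comparisons of included with non-included patients and of completers with dropouts. The risk is one of interpretation.

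A reader might also take 81% to 99% as the plan's error rate. Those figures are the power to detect correlations that were assumed. They become misclassification rates only if significance is read as modification, and weaker factors give rates as low as 11%.

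Nor can it be said that everything needed exists in both arms. This is shown for the baseline characteristics and the outcome, although Table 1 has service use recorded continuously in the intervention group and every three months in controls. It is not shown for adherence: Table 1 names no measure of it, and if it means adherence to the programme, controls have no counterpart. The one-arm criticism therefore applies to three of the four variables.

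Finally, the valid analysis has little power. That stands, but it does not make the one-arm coefficient an estimate of modification.

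**Conclusion.** The point holds in a limited form. The article states a population and a method for its third aim that cannot show who benefits more or less from the programme. This is a fixed choice, not a detail left to a later plan. A purely prognostic factor is significant in about 11% to 95% of trials for assumed log effects of 0.10 to 0.50, or 81% to 99% for assumed correlations of 0.2 to 0.3, against the nominal 5% ("The level of significance is set at 0.05, two-tailed") for an interaction test. A masked modifier is found only about 5% of the time. These figures rest on assumed prognostic effects, an evenly split binary factor, 200 patients per arm with complete data, and the log-normal scale of the sample-size calculation. The algebra, that one arm gives β + γ and not γ, needs none of these assumptions about size or prevalence. On the prognostic reading the fault is smaller: half the sample unused, and prognosis described only under the programme. The matter is confined to a secondary aim and leaves the primary comparison as it was.

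**What to change.** State whether the third aim concerns modification of the programme's effect or prognosis.

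- **Modification:** for treatment history, diagnosis and social support at baseline, fit a model in all randomised patients with arm, characteristic and arm-by-characteristic interaction. Name the scale, because an interaction absent on the log scale can be present in days. Report estimates with confidence intervals, labelled exploratory.
- **Prognosis:** use both arms with arm in the model, and replace the word *modify*.
- **Adherence during follow-up:** define it, say how and in whom it is measured, and analyse it separately as descriptive or as a possible mediator, without calling it a modifier.

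For the baseline characteristics this changes analysis wording only, with no new data or visits. The cost is precision: about 30% power for an interaction as large as the planned main effect, so intervals will be wide and a null interaction should not be read as evidence of a uniform effect.
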